**Primary Endpoints**

- Change in *K*i, the influx constant that describes the rate of [18F]FDG uptake into the right middle lobe, between baseline and post-endotoxin scans.
- Absolute *K*i after endotoxin

**Secondary Endpoints**

- BAL cell counts (total and neutrophil counts)
- BAL PPAR- γ transcriptional activity
- BAL LXA4, LTB4, IL-8 and TNF-α levels (measured by ELISA)
- BAL 5-LO, 15-LO, PPAR-γ mRNA levels
- Urine LTE4 levels

**Exploratory Endpoints**

- CT density (in Hounsfeld Units, HU)
- Airway thickness
- Respiratory-gated standard uptake value (SUV)
- Presence of TLR4 polymorphisms

1. **SUBJECTS**
   1. **Inclusion Criteria**

- Healthy man or woman, any race or ethnicity, age 19 – 44 years old
- Screening FEV1 and FVC >= 90% of predicted
- Screening oxygen saturation by pulse oximetry >97% on room air
- Capable of lying still and supine within the PET/CT scanner for ~1.5 hours
- Capable of following instructions for breathing protocol during CT portion of PET/CT
- Able and willing to give informed consent
- BMI < 35
  1. **Exclusion Criteria**
- Pregnancy (confirmed by qualitative urine hCG pregnancy test)
- Lactation
- History of cardiopulmonary disease
- Currently taking any prescription medications
- History of tobacco use or illicit drug use within the past year
- Presence of implanted electronic medical device
- Enrollment in another research study of an investigational drug
- Known allergy to pioglitazone or zileuton
- Known allergy to both trimethoprim/sulfamethoxazole and amoxicillin
- Known allergy to drugs routinely used during bronchoscopy
- History of chronic active liver disease or acute liver disease within the past 3 months
- SGOT >47 IU/L, SGPT > 53 IU/L, or bilirubin > 1.1 mg/dl
- Inability to lie flat for 1.5 hours for PET/CT scans or follow breathing protocol instructions for the CT portion of the PET/CT
- Prior research-related radiation exposure within the past year such that participation in this study would result in exposures that exceed the limits as defined by the FDA RDRC regulations (21 CFR 361.1)
  1. **Women of Child-Bearing Potential**

We will confirm pregnancy test results in all women of child-bearing potential screened for this study. Women who meet the following criteria may also be enrolled without a screening pregnancy test:

- Post-menopausal status defined as women who are 40 years of age or older and have been amenorrheic for at least 2 years
- Women who have had a hysterectomy and/or bilateral oophorectomy
- Women who have been surgically sterilized with no unintended pregnancies for at least 2 years after the procedure
  1. **Number of Subjects**

We plan to screen up to 51 healthy volunteers to enroll 29 volunteers total. Based on our prior experience with this protocol, we anticipate that ~37% of those screened will not be enrolled either due to unwillingness to participate or failure of screening procedures. After enrollment, we anticipate an 18% dropout rate. Therefore, we plan to screen up to 51 people total, anticipating that 29 will pass the initial screening tests and proceed with study procedures, and 5 will drop out after beginning study procedures, leaving 24 volunteers receiving endotoxin who complete the protocol. This will give us N=6 per group. Enrollment will be stopped when the requisite number of volunteers is recruited.

Additionally, we will obtain deidentified BAL cells and fluid from healthy volunteers in previous trials who have already given consent for their use in general research to use as a comparator for the BAL measurements obtained in this trial.

- 1. **Subject Withdrawal and Replacement**

Subjects who do not complete the protocol-required procedures in their entirety will be replaced to ensure adequate evaluable data are obtained. Subjects are free to withdraw from the study at any time for any reason. Attempts will be made to discuss with the subject the reasons for withdrawal and to continue with the planned study evaluations, with the subject’s consent. No subject will be enrolled twice in this trial.

1. **STUDY PROCEDURES**
   1. **Screening**

All volunteers who give informed consent will undergo a physical exam and have heart rate, blood pressure, respiratory rate, and body temperature recorded. Bloodwork, including complete blood counts, routine chemistries, liver function tests, and coagulation parameters, a urinalysis, and a serum pregnancy test will be obtained. Blood and urine samples will also be obtained for research lab assays in all volunteers. Chest radiography, electrocardiogram and pulmonary function tests (PFTs) will also be obtained. Anyone with any history of cardiopulmonary disease will be excluded.

## Outpatient Drug Treatment

Each volunteer receiving endotoxin will take the following:

- Pioglitazone 45 mg or matching placebo by mouth once daily for 2 weeks prior to admission.
- Zileuton 600 mg or matching placebo by mouth with food qid for 5 days prior to admission.

Volunteers enrolled to undergo BAL only will not be treated with any medications, including placebo.

- - 1. Justification for Dosing

There are no data indicating what dosing regimen for pioglitazone would be optimal for specifically reducing lung inflammation in humans. Several clinical trials in patients with diabetes have demonstrated decreases in human serum C-reactive protein levels with pioglitazone treatment (45 mg/day) for 8 weeks or longer. One study evaluated the ability of pioglitazone to reduce inflammatory markers and vascular changes in response to systemic endotoxin administration in healthy volunteers[68](#_ENREF_68). This particular study did not report any significant impact on TNF-alpha or IL-6 production in the blood at 2 or 4 hours after endotoxin in healthy volunteers who had been taking 60 mg of pioglitazone daily for 9 days. Since pioglitazone serum levels reach steady-state only after 7 days of drug administration, it is possible that the volunteers did not take the drug for a long enough period of time to have an anti-inflammatory effect. We also know that responses in the lungs to endotoxin may differ from that in the systemic circulation[69](#_ENREF_69), so while this study provides a benchmark for determining the dose for this study, the results may not be reflective of what would happen in the lungs after endotoxin exposure. Two studies have reported 9-day dosing in healthy volunteers at 45 and 60 mg per day without any serious side effects. Clinical trials of 8 and 12 weeks’ duration have been conducted in patients with diabetes with pioglitazone without serious side effects attributable to the drug. Based on the available information we have about pioglitazone, we have chosen to give volunteers 45 mg daily for 2 weeks for this particular study.

For zileuton, pharmacokinetic studies have shown that q6hr dosing of the immediate-release tablets achieves the best levels of drug over time[71](#_ENREF_71). One study demonstrated that LTB4 production was completely inhibited after swine dust exposure in healthy volunteers treated with 600 mg q6hr of zileuton for 5 days prior to exposure[72](#_ENREF_72). Therefore, we will use this same dosing regimen for 5 days prior to endotoxin instillation. We do not expect either drug to interfere with the metabolism of the other as they are metabolized by different cytochrome P450 enzymes.

All volunteers treated with study medications will receive at minimum daily phone calls during the 2 weeks prior to endotoxin instillation to verify full compliance with the outpatient pioglitazone and zileuton treatments. Video conferences to document compliance will be performed whenever possible. If any evidence of noncompliance with the outpatient drug regimen is discovered before inpatient study procedures begin (which will include inability to contact the volunteer during the outpatient treatment period for compliance verification), the volunteer will be withdrawn from the study.

- - 1. Drug Preparation

Pioglitazone and zileuton will be obtained through commercial sources. Pioglitazone will be overencapsulated with a size 00 capsule (Gallipot, Inc., St. Paul, MN) for blinding and cushioned with lactose monohydrate NF (Spectrum Co., Gardena, CA). Zileuton tablets will be crushed and then overencapsulated with a size 000 gelatin capsule (Gallipot, Inc., St. Paul, MN) for blinding. Matching placebo pills containing lactose for both pioglitazone and zileuton will also be created. All encapsulation and the distribution of pills into a medication container will be performed by the Investigational Drug Service of the Barnes-Jewish Hospital Pharmacy, which has supported our two prior clinical trials. Endotoxin will be prepared and administered as previously described.

- - 1. Medication Diary

Volunteers will be asked to document when they take the pioglitazone/placebo and zileuton/placebo pills on a spreadsheet (Appendix III). They will be asked to write the time that they took the pills required in each box on the spreadsheet.

- 1. **Bronchoscopic Administration of Endotoxin and Bronchoalveolar Lavage**
     1. Bronchoscopy and endotoxin administration

The volunteer will be given 2 doses of either trimethoprim/sulfamethoxazole or amoxicillin, approximately 12 hours apart, prior to bronchoscopy. The volunteer will be continuously monitored by heart rhythm, oxygen saturation, and non-invasive blood pressure monitoring and will receive pre-medications for conscious sedation according to standard protocols through the Barnes-Jewish Hospital Bronchoscopy Suite (Appendix I). A 5F balloon-tipped monitoring catheter will be inserted via a fiberoptic bronchoscope to occlude a single lung segment (usually the lateral segment of the right middle lobe). Endotoxin (4 ng/kg, in 2 ml water) will be administered through the distal port of the catheter. The catheter will be flushed with 10 ml of normal saline, followed by 10 ml air. The catheter will be kept in place for 30 sec, after which the balloon will be deflated. The catheter and bronchoscope will then be withdrawn and the head of the bed raised to 30o. Post-procedure monitoring, including frequent vital signs and oxygen saturation monitoring (q 30 min x 4 hr, q 1 hr x 4 hr, and then q 4 hr until completion), will take place in the CRU.

- - 1. Drug preparation

The endotoxin (E. coli O:113, Reference Endotoxin) will be reconstituted with sterile water to a final concentration of 2,000 endotoxin units/ml. The dose of 4 ng/kg will be prepared to a final volume of 2 ml. [name] is the current Sponsor-Investigator for IND #100042 for endotoxin administration to humans.

- - 1. Bronchoalveolar lavage (BAL)

After wedging the bronchoscope into the same segmental airway used for endotoxin administration, three sequential 50 ml volumes of sterile warmed (37°C) normal saline will be instilled through the suction channel of the bronchoscope. BAL fluid will be recovered by gentle aspiration after each aliquot, pooled, and kept on ice. Cells obtained by BAL will be separated from the fluid immediately, fixed, and stained with Wright-Giemsa stain for determining cell counts and assayed for [3H]deoxyglucose ([3H]DG) uptake. The BAL fluid itself will be frozen and stored for later cytokine analysis.

- 1. **PET-CT Imaging with [18F]FDG**
     1. Imaging acquisition protocols:

Imaging studies will be performed on [name] of Barnes-Jewish Hospital in the Center for Clinical Imaging Research (CCIR). Imaging data will be acquired on a Siemens Biograph 40 TruePoint Tomography PET/CT scanner and will be reconstructed using filtered back projection. Research participants will be fitted with a pneumatic bellows device that wraps around the patient’s abdomen and positioned supine in the scanner. The participant may also be fitted with a vacuum body bag on which they will lie during the scan; the bag will be fixed to a standard flat table to minimize motion artifacts during the scan. Foam pads and pillows will also be used to ensure comfort during the scan. To assist study staff with positioning participants in an identical fashion for greater reproducibility during the second PET/CT scan, a photograph of the body with the face covered/de-identified will be taken and will then be deleted once the second scan is completed. A low-dose CT scan (30 effective mAs) will be obtained with placement of the participant such that the right middle lobe is imaged. The CT scan will be obtained at normal end-expiration, as several studies have demonstrated that this protocol minimizes misregistration artifact. After completing the transmission scan, 10 mCi of [18F]FDG will be injected i.v. at the start of a 60-minute dynamic scan acquisition and the i.v. catheter flushed with 10 ml saline. Imaging will be obtained with the following framing schedule: 24 5–sec, 6 3-minute and 8 5-minute frames. The pneumatic bellows device simply records movement of the abdomen to obtain respiratory phase information during the PET scan for image processing after completion of the PET imaging acquisition. Blood samples will also be collected during this time to determine the “input function.” A second end-inspiration, low-dose CT scan (50 effective mAs) will also be obtained at the end of the PET/CT acquisition. Additional information is located in Appendix II.

- 1. **Blood Collection**

In addition to the screening procedures as described in Study Procedures for Specific Aim 1, an additional 16 ml of blood will be collected at the screening visit, when the volunteer is admitted to the Clinical Research Unit (CRU, formerly GCRC), at 6 hours after the endotoxin instillation, and again at the time of the second PET scan. White blood cells will be isolated from these samples for determination of [3H]DG uptake (since we do not expect neutrophil activation peripherally, these will serve as a negative control for [3H]DG uptake in the cells collected by BAL). We will also assay for CD11b expression in the cells (specifically in the neutrophils) using flow cytometry. A portion of these blood samples will also be sent for standard blood counts and lab chemistry, including C-reactive protein determination, to confirm that no systemic inflammation is induced by the endotoxin. The levels of the different leukotrienes and other levels of cytokines that are impacted by the drug treatments (which includes several of the secondary endpoints) will be tested by ELISA in the blood obtained at these time points. These markers will serve as internal negative controls for the same assays to be performed on the BAL samples. The samples obtained at 6 hours after the endotoxin will be assayed for inflammatory markers and cytokines as well to further determine whether any systemic response from the endotoxin is noted.

- 1. **Photographing of Bronchoscopy Procedures**

Photographs of the airways only will be obtained during each bronchoscopy procedure. There will be no pictures of facial or other features that might provide the potential for breach of confidentiality. The videos will be identified by code numbers only; the master list will be kept in a location separate from the videotapes. While the study is active, photographs will be stored in a secured location in the investigator’s office. Only research team members will have access to these photographs. These photographs will be stored indefinitely but all identifying source documents will be destroyed 5 years after the research is completed.

- 1. **Specific Procedures Timeline for Volunteers Receiving Endotoxin**

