**Trial Design**

This is a single center, prospective, single-blind placebo-controlled clinical trial. Twenty-four healthy volunteers will be recruited sequentially into the following four treatment groups in this order: pioglitazone plus oral placebo, zileuton plus oral placebo, pioglitazone plus zileuton, or two oral placebos. All volunteers will be blinded to the study drugs. They will then receive endotoxin instilled bronchoscopically in the right middle lobe. Enrolled volunteers will receive their assigned drug treatment as an outpatient and then undergo a baseline FDG-PET scan on Admission Day 1, receive endotoxin on Admission Day 2, and undergo a post-endotoxin FDG-PET scan followed by bronchoalveolar lavage (BAL) on Admission Day 3. Deidentified tissues from healthy volunteers who donated them for future research use will also be obtained for comparison.

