**Day 1:**

1. The volunteer will be admitted to the CRU.
2. Two (2) intravenous catheters will be started, one in each arm. Both catheters will be saline locked or maintained as continuous i.v. with normal saline at a keep-vein-open drip rate (10-20cc/hr).
3. Blood will be drawn for baseline testing, including screening labs and specific research assays for this study. A portion of this blood will also be tested for the TLR4 polymorphism (exploratory endpoints). A small drop of blood will also be taken to check a blood glucose level. A urine sample will also be obtained for research lab assays.
4. A urine pregnancy test will also be obtained, if applicable, to confirm non-pregnancy prior to [18F]FDG administration.
5. FDG-PET/CT scan will be obtained followed immediately by a second CT scan*.* The volunteer will have been instructed to be NPO for at least 4 hours prior to the PET scan.
6. Twelve hours before the bronchoscopy is scheduled, the subject will receive one tablet of oral sulfamethoxazole-trimethoprim (80/400) or oral amoxicillin (500 mg.) by mouth.
7. The volunteer will be NPO after midnight in preparation for bronchoscopy the following morning.
8. Pioglitazone/placebo will be given once daily and zileuton/placebo will be given qid until the morning of Day 3.

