**Day 2:**

1. The volunteer’s temperature will be checked twice during the hour before their bronchoscopy.
2. One hour prior to bronchoscopy, the volunteer will receive a second dose of one tablet of the oral antibiotic: sulfamethoxazole/trimethoprim (80/400) or amoxicillin (500 mg.).
3. The volunteer may receive pre-procedure medications (Demerol, Vistaril), before the bronchoscopy.
4. During the bronchoscopy, endotoxin 4 ng/kg will be instilled into a middle lobe segment of the right lung as described above. The volunteer’s vital signs and oxygen saturation will be monitored closely. Oxygen will be administered to maintain their saturation level per protocol.
5. Once the volunteer returns to his/her room at the CRU, s/he will be observed per protocol for the rest of the day. These observations include: checks of vital signs, oxygenation, and symptoms (q 30 min x 4 hr, q 1 hr x 4 hr, and then q 4 hr until completion).
6. After the bronchoscopy, the i.v. fluids will be maintained until the volunteer can tolerate oral medications and nutrition.
7. Acetaminophen will be administered as needed.
8. The volunteer will be NPO after midnight in preparation for the PET scan and BAL the next day.
9. I.v. fluids will be given beginning at midnight to maintain hydration while volunteer is NPO.

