*Rare***:** Rare reactions that have been reported include racing heartbeat, irregular heartbeat, eye pain, blurred vision, sensitivity to light, water retention, rash, angioedema (swelling around eyes and throat), numbness, cough, bloody nose, shock, mental depression, excitement, sedation, coma, agitation, hallucinations, or seizures.

**Medications used during bronchoscopy for sedation** (each participant may receive one or more of these): Midazolam HCl (Versed) and Fentanyl:

*Likely:*Common side effects include pain at injection site, hiccups, low blood pressure, slow heartbeat, drowsiness, nausea, vomiting, constipation, or slower breathing.

*Less Likely:* There is a slight chance that participants may experience headache, cough, blurred vision, dizziness, lightheadedness, abdominal cramps, difficulty breathing, excitement, confusion, loss of memory, irregular heartbeat, or their heart could stop beating.

*Rare:* Rare reactions that have been reported include convulsions, rash, wheezing, cold and clammy skin, difficulty urinating, rapid heartbeat, or mental confusion.

**Test drugs.** The following drugs are commercially available and FDA-approved. They are designated “test” drugs in the context of this research study.

Pioglitazone:

Adverse reactions reported for pioglitazone are based on chronic administration (at least 16 weeks, typically 26 weeks or longer) in patients with diabetes. It is expected that these reactions will be less likely with the 14-day total treatment protocol required for this study.

*Less Likely:* Upper respiratory tract infection, headache, sinusitis, myalgia, pharyngitis.

*Rare:* Hypoglycemia, heart failure, edema, pain in extremity, back or chest (these were seen with chronic administration of the drug in patients with diabetes; these are expected to be highly unlikely in healthy volunteers receiving this drug for 2 weeks). An increased risk of bladder cancer has been observed in patients taking this drug for at least 12 months or longer.

Zileuton:

Adverse reactions reported with zileuton are based on chronic administration (12-week treatment or longer). It is expected that these reactions will be less likely with the 5-day total treatment protocol required for this study. Small studies with treatment periods similar to the one used in this protocol have not reported adverse effects related to zileuton treatment.

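### The risk section's 5-day zileuton and 14-day pioglitazone totals leave out the inpatient doses, and the zileuton start and spacing are each stated two ways

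*Protocol*

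**What the plan says.** **Outpatient instruction.** Protocol section 4.2 (Outpatient Drug Treatment) says "Zileuton 600 mg or matching placebo by mouth with food qid for 5 days prior to admission". The Specific Procedures Timeline repeats this. Pioglitazone is taken once daily for two weeks, also counted back from admission.

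**Rationale.** Under Justification for Dosing, the protocol prefers q6hr dosing on pharmacokinetic grounds. It cites a study of volunteers "treated with 600 mg q6hr of zileuton for 5 days prior to exposure" and concludes: "Therefore, we will use this same dosing regimen for 5 days prior to endotoxin instillation". The Trial Design summary says that volunteers "receive endotoxin on Admission Day 2", the day after admission.

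**Inpatient continuation.** The Day 1 timeline gives pioglitazone once daily, and "zileuton/placebo will be given qid until the morning of Day 3". Day 3 confirms a last morning dose of both drugs. The procedures table marks study drug on Days 1, 2 and 3.

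**Fasting.** Volunteers fast from midnight before the Day 2 bronchoscopy and again before the Day 3 scan and lavage.

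**Risk section.** Under Test drugs in 5.6.3, pioglitazone reactions are expected to be "less likely with the 14-day total treatment protocol required for this study" and zileuton reactions "less likely with the 5-day total treatment protocol required for this study". The comparison is with chronic use: at least 16 weeks for pioglitazone and 12 weeks or longer for zileuton.

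**The concern.** Two kinds of statement do not agree with the schedule.

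The first is the total exposure. It is used to tell healthy volunteers and oversight bodies how long they take two drugs, one of which has severe liver injury among its rare risks. Such a figure should equal what the schedule delivers.

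The second is the zileuton regimen. It has two starting points (admission or endotoxin) and two descriptions of spacing (q6hr in the rationale, four times daily with food in the instruction). Section 4.2 withdraws a volunteer on any evidence of noncompliance with the outpatient regimen, so that regimen must have one meaning. A volunteer who starts four days before admission meets the endotoxin-anchored wording and fails the admission-anchored one.

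Hypothesis 3 in the Specific Aim presupposes effective 5-LO inhibition, so the timing of zileuton around the challenge should be clear and documented.

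**Working it through.** **Inputs, all from the protocol.** Zileuton 600 mg, four doses a day under either qid or q6hr; 5 days before admission (4.2) or before endotoxin (Justification for Dosing). Pioglitazone 45 mg once daily for 14 days before admission. Endotoxin on Day 2. Both drugs continue on Days 1 and 2, with a last dose on the morning of Day 3.

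**Assumption.** All four zileuton doses are taken on Day 1 and on Day 2, and one on Day 3.

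**The stated totals.** Zileuton: 5 × 4 = 20 doses (12,000 mg). Pioglitazone: 14 × 1 = 14 doses (630 mg). These match the outpatient phase alone, counted back from admission.

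**The totals from the schedule.** Doses = outpatient doses + Day 1 + Day 2 + Day 3 morning.

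| Reading | Doses | Calendar days | Against stated total |
|---|---|---|---|
| Zileuton, 5 days before admission | 20 + 4 + 4 + 1 = 29 (17,400 mg) | 5 + 3 = 8 | 29/20 = 1.45 |
| Zileuton, 5 days before endotoxin (4 outpatient days + Day 1) | 16 + 4 + 4 + 1 = 25 (15,000 mg) | 4 + 3 = 7 | 25/20 = 1.25 |
| Pioglitazone | 14 + 1 + 1 + 1 = 17 (765 mg) | 14 + 3 = 17 | 17/14 = 1.21 |

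**Sensitivity.** If three inpatient zileuton doses were missed (an assumption), the counts would be 29 − 3 = 26 and 25 − 3 = 22. Both still exceed 20.

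**The two starting points.** Full days of zileuton before the day of endotoxin: 5 + 1 = 6 (24 doses) counting from admission, against 5 (20 doses) counting from endotoxin. The instruction therefore gives one day more than the rationale.

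**Spacing.** Both wordings give 4 × 600 = 2,400 mg a day. They differ only in how the doses are spread over 24 hours and in the food condition.

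**Fasting.** The Day 2 timeline gives an oral antibiotic tablet one hour before bronchoscopy, within the fast. The Day 3 timeline gives study drug in the morning, also within a fast. No corresponding line covers study drug on the morning of Day 2, before endotoxin. The medication diary is scheduled for the outpatient period only.

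**The case against.** **The comparison with chronic use survives.** The risk section contrasts a short course with 12 weeks (84 days) or more of zileuton and 16 weeks (112 days) or more of pioglitazone. Eight days against 84, or 17 against 112, leaves the direction intact. This stands: the totals are wrong, but the conclusion drawn from them is not overturned.

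**The regimens may be closer than they look.** Daily dose is identical, and the diary spreadsheet in Appendix III, not shown, may fix clock times. This stands in part. The rationale relies specifically on q6hr spacing and calls the regimen the same, while the instruction does not say q6hr.

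**The condition of taking zileuton with food is not contradicted in hospital.** It appears only in the outpatient instruction; the inpatient line says only qid. This stands. The fasting point is a handling rule left unstated for Day 2, not a contradiction.

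**A check on 5-LO already exists in part.** BAL LTB4 is in the two-way treatment-effect ANOVA. Urine is collected at screening, Day 1 and Day 3, and urine LTE4 is a named secondary endpoint. This stands. Section 6.2, however, uses the urine variables only in correlations with Ki, and an analysis plan not shown may add more.

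**A stronger reading is tempting.** A reader might infer that study drug is withheld until after bronchoscopy, so that the challenge falls in a long dosing gap and a null zileuton or combination result could be put down to the schedule. The documents do not support this. The Day 2 line "the i.v. fluids will be maintained until the volunteer can tolerate oral medications and nutrition" governs fluids and does not delay study drug. Tablets are given during fasts elsewhere in the timeline, and qid dosing is ordered throughout Day 2. The protocol gives no half-life or clock times from which to calculate a gap. The difference in starting points gives more zileuton before the challenge, not less.

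**Conclusion.** The stated total exposures are wrong on the protocol's own schedule. Zileuton is 29 doses over 8 calendar days (25 over 7 if counted from endotoxin) against 20 over 5, and pioglitazone is 17 doses against 14. The excesses are 45% (or 25%) and 21%. They assume full inpatient dosing; the zileuton excess remains with three missed inpatient doses.

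The zileuton start is stated two ways, one day apart. The claim of using the cited study's regimen does not match the written instruction on spacing. How the Day 2 study-drug dose before endotoxin is handled during the fast is not stated.

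These are errors of consistency in dosing and risk text. They do not change sample size, power or alpha, and they do not show that volunteers would be under-dosed at the challenge. They are worth correcting because the risk statement concerns healthy volunteers, and because a withdrawal rule depends on a regimen that can be read two ways.

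**What to change.** 1. Reconcile the procedures table, section 4.2 with its Justification for Dosing, the Outpatient Drug Treatment and Day 1 to Day 3 timelines, and 5.6.3 into one schedule. It should state the interval, the food condition, the event from which the 5 days are counted, and how study drug is handled during each fast, identically for active drug and placebo. The sponsor must decide which version applies; none is recommended here. If the final schedule differs from the cited study's, the rationale should say so.
2. Correct the total-exposure figures in 5.6.3, and any matching participant-facing risk text, so that they include Days 1 to 3.
3. Record the time of the last study-drug dose before endotoxin for every volunteer.
4. Add urine LTE4 to the two-way treatment-effect ANOVA in section 6.2, with its time point named, as the check that 5-LO was inhibited.

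**Cost.** A wording amendment, which section 7.2.1 requires the IRB, RDRC and FDA to approve; one field on the case report form; and one more variable in a planned analysis, from samples already collected. The stated exposures become longer.
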